#### Analysis for Specific Aim 2: RE-AIM implementation framework

In this mixed-methods study, Specific Aim 2 will be assessed using the RE-AIM framework for implementation trials [80]. A full list of metrics, separated by each domain of the RE-AIM framework, is presented in Table 1. Additional details regarding the supervision and audit structure for MLPs and CHWs can be found in Additional files 1 and 2.

For the maintenance of the intervention, we will assess the costs of the intervention, using the Joint Learning Network methodology [85]. Cost data will be analyzed and presented (Table 1) to help program planners and policy-makers understand the implications for possible scale of a similar intervention by the government or other entity in the future.

For quantitative data within Specific Aim 2, a similar methodology of generalized estimating equations, as already described in Analysis for Specific Aim 1: effectiveness, will be applied. Data will be assessed at 3-month intervals.

For qualitative data within Specific Aim 2, analysis will be ongoing and iterative, so as to continually inform further qualitative data collection, focusing on timely and relevant implementation issues. Data from KIIs and FGDs will transcribed and coded using grounded theory methodology [88, 89]. NVivo software will be used for qualitative data analysis [90].

## Discussion

### Ethical approval and consent

This study has been approved by the Ethical Review Board of the Nepal Health Research Council (#177/2018). Within the study, all patients will provide verbal informed consent to have their de-identified data analyzed and published. Care provision will be unrelated to consent, and there will be no difference in care provision based on consent status. Verbal informed consent will also be provided by all KII and FGD participants. No incentives will be provided to study participants, to avoid any conflict of interest or coercion to participate. Protocol modifications will be promptly communicated to the IRB and on the trial registry website by members of the research study team.

### Safety considerations

There are minimal risks posed to patients, staff, or other key informants. The predominant risk is disclosure of protected health information, and/or qualitative data from KIIs or FGDs. All patient information will be stored on secure databases, and data access privileges will be heavily restricted. Unless otherwise deemed necessary for a specific analysis, all analyses will be conducted using a limited dataset. Qualitative data will be stored and protected as already described.

### Data sharing

All de-identified data from this study will be made publicly available for other researchers to analyze at their discretion in the future, to further this field of research. De-identified summaries of qualitative data will be made available as well.

### Dissemination plan

Domestically within Nepal, 6-monthly update meetings will be held between researchers and the Ministry of Health and Population to review ongoing results. When completed, results of the study will be presented at the annual National Summit of Health and Population Scientists, organized by the Nepal Health Research Council, and at other relevant international conferences. Peer-reviewed publications will be drafted for international dissemination.

## Trial status

At the time of manuscript submission, the study is currently not yet recruiting participants. Participant enrollment is anticipated to commence in February 2020 and is planned to continue for 1 year. Intervention deployment took place between July 2018 and will conclude in January 2020. This is study protocol version 1.2 and the version date is December 6, 2019.

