**Methods:**

A 12-month, population-level, type 2 hybrid effectiveness-implementation study will be conducted in rural Nepal to evaluate an integrated noncommunicable disease care management intervention within Nepal’s new municipal governance structure. The intervention will leverage the government’s planned roll-out of the World Health Organization’s Package of Essential Noncommunicable Disease Interventions (WHO-PEN) program in four municipalities in Nepal, with a study population of 80,000. The intervention will leverage both the WHO-PEN and its cardiovascular disease-specific technical guidelines (HEARTS), and will include three evidence-based components: noncommunicable disease care provision using mid-level practitioners and community health workers; digital clinical decision support tools to ensure delivery of evidence-based care; and training and digitally supported supervision of mid-level practitioners to provide motivational interviewing for modifiable risk factor optimization, with a focus on medication adherence, and tobacco and alcohol use. The study will evaluate effectiveness using a pre–post design with stepped implementation. The primary outcomes will be disease-specific, “at-goal” metrics of chronic care management; secondary outcomes will include alcohol and tobacco consumption levels.

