### Study populations

For primary quantitative outcomes, the study population will include adult patients (≥ 18 years of age) who qualify for a diagnosis of hypertension, type II diabetes, and/or COPD, according to WHO-PEN guidelines, and are engaged in longitudinal care by Nyaya Health Nepal’s team in Achham and Dolakha. The study will limit enrollment to the catchment areas served by both the facility-level and CHW-level services deployed by Nyaya Health Nepal. Study participants will be initially enrolled during facility-based visits at Bayalpata Hospital and Charikot Primary Health Care Center prior to the completion of intervention roll-out, and are considered engaged in longitudinal care if they have at least one follow-up hospital visit after 12 months of their initial visit. Digital health records that link between the facility-based EHR and the CHWs’ mobile-phone applications will be utilized to share patient data across settings, when available. CHWs can identify potential patients in the community and refer them to the facility for diagnosis confirmation, following which they could be included in the study. Patients’ receipt of care will not be contingent upon their enrollment in the study; all patients will continue to receive care per routine service delivery. This represents an exhaustive convenience sampling method as all eligible patients identified at Bayalpata Hospital and Charikot Primary Health Care Center may be enrolled in the study. Exclusion criteria are individuals planning to migrate from the study area prior to 12 months of exposure to the intervention, or individuals explicitly requesting exclusion from the study or declining to consent (see Additional file 3) for the study.

For implementation components, staff members, patients, community leaders, and government officials will be approached for key-informant interviews (KIIs) and focus group discussions (FGDs), as described in the following.

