### Study design

This is a prospective, mixed-methods type 2 hybrid effectiveness-implementation study to evaluate an integrated NCD care management intervention. We plan to apply both qualitative and quantitative methods in a complementary manner [79], in order to meaningfully assess both patient-level and population-level outcomes and the effectiveness of the implementation strategy. We will study the intervention’s impact on patients’ disease management outcomes after 12 months of being enrolled in NCD care using a pre–post design across both sites:
We will study the implementation of the intervention utilizing both quantitative and qualitative methods applying the RE-AIM (Reach, Effectiveness, Adoption, Implementation, Maintenance) framework [80].

Data collection is developed and integrated within the routine course of delivering care, which is an ethical, acceptable, and affordable approach in this setting. See Fig. 1 for a trial flowchart and Additional file 4 for a SPIRIT research reporting checklist. It is not feasible nor ethically acceptable to obtain data on a comparison (control) group in this population. Given the lack of national or local NCD systems, no data are available from other sources prior to the start of the study.

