#### Qualitative data

Qualitative data will be used for Specific Aim 2 (Table 1). Staff members, patients, community leaders, and government officials will be approached for KIIs and FGDs. Purposive sampling will be used, aiming to maximize heterogeneity across sex, socioeconomic position, healthcare issues, geographic location, age, caste class, and other attributes. For each group, five key informant interviews will be conducted at each time point, as described in the following. One focus group discussion per group will be conducted at each time point.

KII and FGD guides will be developed in advance, and will vary across the study period, exploring specific topics of concern. A locally validated, seven-domain framework of healthcare delivery analysis will be used to inform data collection [86]. These seven domains include health service operations, supply chains, equipment, personnel, outreach, societal factors, and structural factors. Qualitative data collection will focus on these areas to assess the implementation of the intervention.

FGDs and KIIs will occur prior to the initiation of the intervention, and at intervals of 6 months throughout the study period, to assess ongoing implementation status. All sessions will be conducted in Nepali. All qualitative data will be stored on a Research Electronic Data Capture (REDCap) database [87]. REDCap user access will be defined so that researchers only have access to de-identified study data. Any paper copies of data forms will be stored in locked cabinets inside locked rooms at district facilities. Once all data are fully transcribed and validated for quality, all paper copies will be destroyed. REDCap data will be deleted 12 months after the completion of the study period.

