### Data analysis

#### Analysis for Specific Aim 1: effectiveness

In order to assess the effectiveness of the intervention, as already described, the primary outcome will utilize disease-specific “at-goal” metrics for each of the three study diseases: hypertension, type II diabetes, and COPD. We hypothesize that the integrated intervention will lead to a 10% increase in the “at-goal” status of the combined disease cohorts, over a 12-month follow-up period.

We will use conditional multivariable logistic regression to assess patient outcomes at 12 months of follow-up, adjusting for potential confounding and/or effect modification by patients’ demographics (including age, sex, caste), municipality, district, mean distance to the hospital, and engagement in care (defined as number of facility-based and community-based encounters). We additionally hypothesize a 10% improvement in the status of each of the two secondary outcomes: tobacco and alcohol use, as measured by patient-reported outcomes presented in Table 1.

As a secondary analysis for Specific Aim 1, namely the time-varying nature of the outcomes, we will assess the longitudinal effect of the intervention, as measured in 3-monthly intervals, throughout the study period, compared to baseline statistics at the time of each village-cluster enrollment. Variables will be considered either nominal or continuous (linear effect) predictors, and the generalized linear model framework will be used to estimate effect of time-varying repeated-measure intervention implementation over the several steps of the wedged design. Differential impact from time of intervention will be evaluated with test of month × intervention interaction. Models will be fit using generalized estimating equations, for example, using SAS Proc Genmod, to calculate valid standard errors in the presence of repeated measures over time and possibly correlated outcomes at the municipality level. Assumptions of overdispersion or underdispersion will be examined closely, and an estimated scale parameter or negative binomial models will be used as needed.

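### Trial status places all enrolment after roll-out, which contradicts the enrolment rule in Study populations and leaves the secondary stepped analysis without unexposed periods

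*Protocol article*

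**What the plan says.** All references are to the protocol article.

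- **Trial status** (version 1.2, dated 6 December 2019) gives the calendar: "Intervention deployment took place between July 2018 and will conclude in January 2020", and "Participant enrollment is anticipated to commence in February 2020 and is planned to continue for 1 year".
- **Study populations** says that participants are first enrolled at facility visits "prior to the completion of intervention roll-out". All eligible patients at the two facilities may enter. Enrolment is not restricted to newly diagnosed patients.
- **Abstract, Methods** describes the design: "The study will evaluate effectiveness using a pre–post design with stepped implementation".
- **Study design** sets the primary contrast as the intervention's impact on disease outcomes "after 12 months of being enrolled in NCD care using a pre–post design across both sites". It adds that a comparison group is neither feasible nor ethical, and that other sources hold no data from before the study.
- **Analysis for Specific Aim 1** hypothesises that the intervention produces a 10% increase in at-goal status over 12 months. A secondary analysis in 3-month intervals, referred to a baseline at each village cluster's entry, is to "estimate effect of time-varying repeated-measure intervention implementation over the several steps of the wedged design" and to test a month × intervention interaction.

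**The concern.** The enrolment rule and the calendar describe the same study and point in opposite directions. A patient enrolled from February 2020 onwards enters after the stated end of roll-out, not before it. The eligible cohort is therefore undefined as the text stands.

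The order of these events also decides what can be analysed. A stepped model learns the intervention effect from periods in which some clusters have the programme and others do not. If all data come from after the last cluster was deployed, there is no such period.

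The primary comparison does not need steps, but the article reads it as the intervention's effect. That reading is weaker when the starting value is measured inside a programme that is already running. At stake are a planned secondary analysis that could not be run and an effectiveness claim that the primary comparison could not carry by itself.

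**Working it through.** **1. Calendar.** Inputs are the two date statements in Trial status and the 12-month outcome in Study design.

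| Event | Dates | Length |
|---|---|---|
| Deployment | July 2018 to January 2020 | 19 calendar months, counting both end months |
| Enrolment | February 2020 to January 2021 | 12 months |
| 12-month outcomes complete | about January 2022 | 24 months from first enrolment, or 8 three-month periods |

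Overlap of enrolment with deployment: 0 of 12 months. Enrolment opens in the month after deployment ends. Patients for whom both the Study populations rule and the Trial status dates hold: none. At the first possible baseline the earliest cluster has had the programme for (2020 − 2018) × 12 + (2 − 7) = 19 months, and the last for about 1 month.

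**2. Stepped model on these dates.** Take the four municipalities (Study setting) and the 8 three-month periods above, which gives 32 municipality-periods. Let X = 1 when a municipality is deployed. On the stated dates X = 1 in all 32.

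- Columns: intercept (1) + period effects (7) + intervention (1) = 9.
- Rank of the design matrix: 8.

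The intervention column equals the intercept column, so its coefficient is not identifiable. This does not depend on how time is modelled, nor on whether the unit is the municipality or the village cluster, because every unit is deployed in every period. Month × intervention equals month × 1, which is month itself, so the interaction cannot be separated from time either.

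**3. The same model with earlier data.** Suppose data ran from July 2018 in 14 three-month periods, with municipalities starting in periods 0, 2, 4 and 6. These start periods are an assumption, because the article gives no step dates. The columns are 1 + 13 + 1 = 15 and the rank is 15, so the intervention term becomes estimable. The obstacle is therefore the calendar, not the form of the model. Full rank shows that an estimate exists. It does not show that four municipalities would give a precise one.

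**4. Primary comparison.** The pairing is each patient's baseline status against status after 12 months in care. It needs no unexposed cluster and can be computed on any calendar. The power figures in Sampling strategy and power calculations are not affected. With N = 1000, difference d = 0.05, discordant proportion p and z = 1.96, power is Φ[(d√N − z√p) / √(p − d²)]:

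- p = 0.40: (1.581 − 1.240) / 0.630 = 0.54, power 0.706. The exact conditional McNemar test gives 0.690, against 69% stated.
- p = 0.10: (1.581 − 0.620) / 0.312 = 3.08, power 0.999, against 99% stated.

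What changes is the meaning of the baseline. From February 2020 it is taken in a deployed municipality. Existing patients may enter, and Study setting says that some noncommunicable disease care has run at the Achham site since 2008. Some baselines may therefore follow the patient's own exposure.

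**The case against.** **The two sections disagree, so neither date can be taken as settled.** Data are extracted from routine health records, and the clock in Study design starts at enrolment in care. Study outcomes also limits the 24-month analysis to those enrolled within 12 months of the study's start, which would be a subset only if enrolment ran longer than the one year in Trial status. First care visits during roll-out, with formal study enrolment from February 2020, would reconcile most of this. The point stands as far as it goes. A reader might infer that unexposed time is zero and that no participant has any pre-intervention period, but the documents do not establish that. They also do not state the reconciling reading: the study is called prospective, and nothing says that records from before February 2020 enter the analysis.

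**Municipal roll-out is not patient exposure.** This stands. A newly diagnosed patient's first visit can precede that patient's own receipt of the intervention. A reader might infer that the primary pre–post contrast fails altogether, but it does not.

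**Attribution is weak in any uncontrolled design, and the article says openly that it has no control group.** This largely stands and would remain after the dates were corrected. It is no answer to the stepped analysis, and it makes a clearly defined baseline more important.

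**The stepped model is only secondary.** True, and it limits the weight of the point. It is still a planned analysis that cannot be run on the stated dates.

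Two further inferences are not supported. One is that regression to the mean alone would exceed the hypothesised 10%. That needs blood pressure distributions that the article does not give, and would cover one of three diseases. The other starts from "FGDs and KIIs will occur prior to the initiation of the intervention" and concludes that the interviews are overdue. The article does not say whether they had already been held, and the ethics approval number carries the year 2018.

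**Conclusion.** The point holds in three parts of different strength.

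1. **Certain:** Study populations and Trial status contradict each other. On the stated dates the overlap is 0 of 12 months and no participant meets the enrolment rule.
2. **Certain if the Trial status dates govern all data:** the secondary stepped analysis and the month × intervention test cannot be estimated (rank 8 of 9 columns, 0 of 32 municipality-periods unexposed).
3. **A matter of interpretation:** the primary comparison can be computed and its power figures stand. On these dates it measures change over 12 months of care under a deployed programme, with some baselines possibly already exposed. It does not isolate the intervention's effect.

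Parts 2 and 3 assume that deployment did end in January 2020, which was still a forecast at the version date, and that no earlier records are used. The article needs correcting before enrolment opens, because who is eligible and which analyses can run both depend on the answer.

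**What to change.** Put Study populations, Study design, Analysis for Specific Aim 1 and Trial status on one calendar, and bring the design sentence in the Abstract into line. There are two ways.

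**(a) Keep the stepped analysis.** State that health records from before and during deployment (from before July 2018 to January 2020) supply the unexposed periods. Give each cluster's roll-out date and include a calendar-time term in the model. Cost: a further query of the same record system and ethics confirmation for the earlier records. It relies on patients who were in care before roll-out, because patients first seen from February 2020 have no pre-roll-out value. The population is therefore different and has to be described as such. It also assumes that usable records exist for that period, which the article does not say.

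**(b) Use only patients enrolled from February 2020.** Delete the stepped analysis and the month × intervention test, and correct the enrolment rule in Study populations. State the primary result as within-patient change over the first 12 months of enrolled care under a deployed programme, not as the intervention's effect. Cost: wording only. The downside is a weaker claim.

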## Data Availability

The datasets supporting the conclusions of the study will be made publicly available in de-identified form upon conclusion of the study. The final trial dataset (in limited identifier format) will be accessible to researchers at the research performance site in Nepal—Nyaya Health Nepal—and co-investigators assisting with data analysis. Participating research institutions will enter into data-sharing agreements (namely between the research performance site in Nepal—Nyaya Health Nepal—and any foreign institutions where investigators are assisting with data analysis) covering terms of access to specific limited datasets; provisions for storing, sharing, and using data; and methods for securing data transfer.

## Abbreviations

CDS: Clinical decision support
CHN: Community health nurse
CHW: Community health worker
COPD: Chronic obstructive pulmonary disease
EHR: Electronic health record
FGD: Focus group discussion
HEARTS: Healthy-lifestyle counselling. Evidence-based treatment protocols. Access to essential medicines and technology. Risk based charts. Team-based care. Systems for monitoring
KII: Key-informant interview
LMIC: Low and middle-income country
MI: Motivational interviewing
MLP: Mid-level practitioner
NCD: Noncommunicable disease
RE-AIM: Reach, Effectiveness, Adoption, Implementation, Maintenance
REDCap: Research Electronic Data Capture
WHO: World Health Organization
WHO-PEN: WHO Package of Essential Noncommunicable Disease Interventions
